## Method

### Aim

We adopt a two-arm randomized controlled trial (RCT) design to investigate whether VR-delivered controlled exposure can complement standard psychological counseling in addressing PSA and general anxiety symptoms among students accessing the UPCS. The findings are expected to provide evidence regarding the effectiveness of integrating VR-based exposure as an adjunct to Exposure and Response Prevention–Acceptance and Commitment Therapy (ERP-ACT) within counseling to manage anxiety and stress in university students.

It is hypothesized that:

Primary Outcome - Students receiving brief psychological counseling supported by ERP and ACT training combined with VR-based exposure exhibit significantly greater reductions in PSA and anxiety levels from baseline (T0) to post-intervention (T1), compared with students receiving standard psychological counseling alone.Secondary Outcome - The two VR components (ERP and ACT) are expected to exert differential effects. Specifically, the relaxation modules should primarily reduce physical tension and physiological arousal, whereas the immersive exposure modules should mainly target the psychological aspects of public speaking, leading to lower fear and reduced perceived mental effort during performance-related scenarios. Physiological data are continuously recorded during each intervention session to assess patterns of arousal and recovery and to examine whether VR-supported counseling is associated with different within-session responses compared with counseling alone.Other Pre-specified Outcome - These benefits are expected to be maintained over time; therefore, students in the VR-ERP and VR-ACT training conditions are expected to continue to exhibit better outcomes at the 3-months follow-up assessment (T2), compared with students receiving standard counseling alone.

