### Design and setting of the study

The study is a two-arm randomized controlled trial with parallel, independent experimental and control groups. Both groups undergo a brief standard counseling program consisting of five individual sessions delivered by trained clinicians within the UPCS. The experimental group receives the same brief standard counseling intervention, complemented by two immersive VR modules delivered through 360° video-based scenarios: (a) a VR–Exposure and Response Prevention (VR-ERP) component providing graded and controlled exposure to anxiety-provoking public-speaking situations, and (b) a VR-Acceptance and Commitment Training (VR-ACT) component offering an ACT-based mindfulness training aimed at down-regulating physiological arousal and enhancing adaptive coping. The control group receives the standard counseling protocol only.

Psychological assessments are conducted at baseline (T0), post-treatment (T1), and at follow-up (T2), allowing evaluation of change over time and between-group differences. Physiological parameters are continuously recorded during each session to capture objective indices of arousal and recovery alongside self-report outcomes. This design enabled testing whether adding immersive, VR experiences to routine counseling provides benefits beyond standard care alone.

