### Interventions

#### Participants

Participants in the control group do not receive VR training but follow the same assessment schedule as the experimental group. Specifically, they complete baseline (T0), post-intervention (T1), and follow-up (T2) evaluations using the same psychological measures. This design allows comparison between intervention and control conditions, thereby isolating the effects of VR training from potential confounding factors such as time and repeated testing effects.

The experimental intervention includes two distinct VR-based training components: (A) VR-ERP, which gradually exposes students to anxiety-provoking situations to prevent avoidance responses, and (B) VR-ACT training, which provides consistent mindfulness practice aimed at enhancing psychological flexibility and value-oriented behaviors. After completing VR-ACT training, participants in the experimental group proceed to a standard counseling intervention.

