#### Experimental arm – VR-based training scenarios

VR is employed for a dual therapeutic purpose:

simulating feared, anxiety-evoking scenarios, thereby enabling both assessment and training of situationally induced anxiety and progressively promoting desensitization to anxiety-provoking stimuli;delivering an ACT-consistent mindfulness training targeting psychological flexibility processes (e.g., contact with the present moment, cognitive defusion, and acceptance), eliciting a grounding response within a digitally generated and safe environment.

VR sessions are divided into three sequential phases (total duration approximately 15 min): Adaptation, Exposure, and Relaxation (Fig. 3).

Adaptation phase (5 min): Participants are guided through brief relaxation and grounding exercises and are familiarized with the VR equipment. Procedures for operating the devices (described in subsequent sections) are explained, and participants are encouraged to become comfortable in the immersive environment to facilitate engagement and reduce novelty-related discomfort during subsequent phases.

Exposure phase (5 min): This phase constitutes the core component of the VR-based intervention. Participants are exposed to simulated public speaking situations embedded within an examination context. Across sessions, task difficulty and social-evaluative stress are gradually increased through systematic manipulation of virtual characters (e.g., number and behavior of avatar instructors and audience members). This graded exposure supports progressive acquisition and practice of skills to manage anxiety and stress related to examinations.

Relaxation phase (5 min): This phase is dedicated to mindfulness practice and rebalancing, aiming to reduce stress accumulated during exposure. Mindfulness practice supports inner awareness and improves emotion and stress management. The relaxation component also facilitates consolidation of the intervention’s effects on anxiety and stress regulation.

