#### VR-ERP

VR-ERP uses 360° 3D videos depicting scenarios such as an exam classroom and an auditorium within a university campus (Fig. 3a–b). Across sessions, variables such as audience size and behavior, professor characteristics, attire (formal vs. informal), and examination committee composition vary. Scenarios are presented according to a gradual hierarchy of challenge; at the student’s discretion, specific scenarios are repeated. Scenarios are selected based on distressing contents identified in the research-intervention literature [29]. During simulations, participant interactions influence the subsequent course of the exposure scenario. Each scenario follows a graded increase in exposure intensity, culminating in an oral exam involving a PowerPoint presentation in the final exposure. Each VR-ERP session is preceded by a VR-ACT session and followed by a 10-minute debriefing intervention providing supportive feedback and guidance to consolidate skills acquired during exposure.

Familiarization session: in the session participants receive a standardized explanation of the VR program’s aims and procedures. They are introduced to the Oculus Quest 3, a consumer-grade standalone VR system consisting of a head-mounted display (HMD) and two handheld controllers. After donning the headset, they complete a brief 5-minute familiarization session to learn basic controls and navigation. This training supports acclimatization to the VR environment, facilitates graded exposure to performance-related stressors, and promotes adaptive regulation of physiological and affective responses within a controlled yet ecologically valid simulation.

Baseline session: the session establishes a physiological reference point preceding implementation of the training. The configuration elicits a controlled anxiogenic response associated with judgment, self-presentation, and evaluation expectancy. Physiological measures provide a baseline stress reactivity index under standardized conditions and support subsequent assessment of training-related modulation of autonomic responses.

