## Discussion

Public speaking anxiety is one of the most prevalent forms of anxiety among students in higher education [30]. Overall, research across countries indicates that public speaking and presentation tasks are among the most anxiety-provoking learning situations in higher education. High proportions of students report significant fear or anxiety in these contexts, and even preliminary evidence suggests that, for some, symptoms can reach clinically meaningful levels [31, 32].

This project attempts to provide university students accessing the UPCS with a safe, controlled, and ecologically valid environment to practice managing PSA in realistic but non-threatening academic contexts, such as exams, research presentations, and oral defenses. Grounded in emotional processing theory [33] and the cognitive-behavioral framework of exposure therapy [34], the intervention leverages a VR-based treatment to elicit anxiety-related responses within a controllable context. This approach allows participants to gradually face and regulate stress while developing adaptive coping mechanisms related to public speaking anxiety. From a scientific standpoint, the project contributes to growing evidence that VR-based interventions can effectively simulate socially evaluative situations, enhancing self-efficacy, emotional regulation, and desensitization processes in individuals with PSA and related forms of performance anxiety [35, 36]. Specifically, the project aims to highlight how the combination of standard counseling with VR-based ERP and ACT-consistent training may enhance therapeutic effectiveness beyond what either approach could achieve alone. By embedding VR-based exposure within an ongoing counseling relationship, the intervention allows feared public speaking situations to be addressed in a graded, controlled, and ecologically valid manner, while simultaneously promoting reflective processing, emotional meaning-making, and values-based through therapist support.

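### The secondary hypothesis of different VR-ERP and VR-ACT effects cannot be tested as a component effect, because the whole experimental arm receives both modules and the in-scenario outcomes it names have no matching measure

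*Protocol article*

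**What the plan says.** The Aim section predicts, as the secondary outcome, that "The two VR components (ERP and ACT) are expected to exert differential effects". The relaxation modules should act mainly on bodily tension and arousal. The exposure modules should act on the psychological side, "leading to lower fear and reduced perceived mental effort during performance-related scenarios". The same item closes with a different question: whether within-session physiological responses differ between VR-supported counseling and counseling alone.

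On design, the article says: "The study is a two-arm randomized controlled trial with parallel, independent experimental and control groups". On the content of the experimental arm: "The experimental group receives the same brief standard counseling intervention, complemented by two immersive VR modules delivered through 360° video-based scenarios". Table 1 ticks both modules in each of weeks 1 to 4 for that arm.

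On sequence, the section on the experimental arm says "VR sessions are divided into three sequential phases (total duration approximately 15 min): Adaptation, Exposure, and Relaxation", with mindfulness practice placed in the last phase. The VR-ERP section says "Each VR-ERP session is preceded by a VR-ACT session and followed by a 10-minute debriefing intervention".

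The listed self-report scales are the PRPSA and the STAI-Y State and Trait, given at T0, T1 and T2. Wristband physiology is recorded in the four intervention weeks. The Statistical analyses section plans mixed models and event-based analyses of the physiology and names no ERP-versus-ACT contrast.

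**The concern.** A hypothesis that two components act differently needs something in the design that separates them: arms that receive one and not the other, a crossover, or at least a randomized order. The article describes none of these. It also ties the exposure component to fear and mental effort felt during the scenarios, and such outcomes need ratings taken at that time.

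What is at stake is the standing of the conclusion. Because the hypothesis is pre-specified, a lower heart rate in the forest scene than in the exam scene could be reported as confirming that ACT works on the body and ERP on the mind. It would show only that a calm scene arouses less than a stressful one. The same attribution reappears in the Discussion as the proposed mechanism, so it is likely to shape how results are read.

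**Working it through.** **1. What the sample size covers.** Inputs from the Sample size section: d = 0.75 for the between-group difference in change, two-sided α = 0.05, power 0.80, dropout 20%. The two-sample t-test gives n = 28.9, so 29 per group (power 0.801), as stated. Dropout: 29 / 0.8 = 36.25, against 36 stated, which agrees to rounding. This calculation concerns one contrast, the VR arm against control.

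**2. Can the components be separated?** For participant i, let E = 1 if VR-ERP is received, A = 1 if VR-ACT is received, and G = 1 in the experimental arm. A model with separate effects is

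Y = b0 + bE·E + bA·A + error.

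The design section and Table 1 give E = A = G for everyone. Then

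Y = b0 + (bE + bA)·G + error,

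so only the sum is estimable. With 36 + 36 participants, the matrix [intercept, E, A] has rank 2 with 3 columns. More participants do not change the rank. In standardized units, a total effect of 0.75 fits bE = 0.75 with bA = 0, or bE = 0 with bA = 0.75, or any other split. Any interaction between the modules and the effect of the debriefing fall into the same sum. A 2×2 layout, by comparison, has rank 4 of 4.

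**3. Does within-session physiology help?** Time-stamped recordings allow a within-person comparison of exposure and relaxation phases. Three things stand in the way of reading it as a component effect:
- The scenes differ in stressfulness by construction.
- The order is not randomized, so recovery from exposure and carry-over are part of the contrast.
- The order is unclear. One section puts mindfulness after exposure; the VR-ERP section puts VR-ACT before it. Arousal in the ACT segment means anticipation under one order and recovery under the other.

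**4. Are the named outcomes measured?**

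| Construct in the hypothesis | Listed measure | During scenarios? |
|---|---|---|
| Physical tension, arousal | PRPSA and STAI State content; HR, HRV, EDA | Physiology only |
| Fear | PRPSA items on fear of audience evaluation | No: T0, T1, T2 |
| Perceived mental effort | None | No |

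**5. What a real test would need.** The documents give no effect size for ERP against ACT, so these are assumptions. For a randomized ERP-only versus ACT-only contrast at 80% power, n per arm before and after 20% dropout is:
- d = 0.75: 29; 29 / 0.8 = 36.25, so 37
- d = 0.50: 64; 64 / 0.8 = 80
- d = 0.25: 253; 253 / 0.8 = 316.25, so 317

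**The case against.** The strongest reply has several parts.

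- **The secondary outcome is not wholly untestable.** Its last sentence is an arm-level comparison, which bundling the modules does not affect. This stands, and the fix builds on it.
- **Fear and tension are not unmeasured.** A reader might infer that they are. The Psychological assessment section says otherwise: PRPSA covers tension and fear of audience evaluation, STAI State covers tension, and physiology is recorded in session. What remains is narrower: no in-scenario fear rating and no mental-effort measure.
- **The Aim does not specify a between-person ERP–ACT contrast, and phase data exist.** True. They are useful descriptively but cannot show which module produced benefit.
- **The order may be less contradictory than it looks.** The adaptation phase already contains some relaxation and grounding, so ACT-like content could fall on both sides of exposure. The sections still need to be reconciled, and the components are inseparable under either order.

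Three stronger readings are tempting but are not supported. One is that the article wrongly claims to isolate VR. Its sentence reads "thereby isolating the effects of VR training from potential confounding factors such as time and repeated testing effects", and a randomized control group on the same assessment schedule does deal with time and repeated testing. Another is that a VR-alone arm is needed because the combination "may enhance therapeutic effectiveness beyond what either approach could achieve alone". That is hedged Discussion text on which no outcome or analysis depends. The third is a percentage for extra contact time in the VR arm. The documents do not state that arm's total contact time, and it is unclear how the familiarization and baseline sessions count, so no figure is firm.

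**Conclusion.** The point holds in limited form. Attribution of PRPSA or STAI change to VR-ERP or to VR-ACT is impossible at any sample size: 0 of the 36 planned experimental participants receive one module alone, and the design supplies one estimable effect where the hypothesis needs two. An analysis plan cannot repair this. Mental effort has no listed instrument, and fear is not assessed during the scenarios. This rests on Table 1 and the design section describing the allocation fully, and on Table 1 listing all planned assessments.

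The primary comparison, its sample size and the arm-level physiological question are untouched. The primary contrast estimates the effect of adding the whole package, debriefing included. That is a legitimate add-on question and should be reported as such. The importance is moderate: it governs what may be concluded from a named secondary hypothesis, not whether the trial can answer its main question.

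**What to change.** 1. Make the secondary hypothesis the arm-level comparison already in the Aim: within-session physiological responses under VR-supported counseling versus counseling alone. Define it on session segments that both arms share. The Statistical analyses section speaks of physiological data from VR sessions, so state that recordings from counseling segments in both arms are used.
2. Label ERP-phase versus ACT-phase comparisons as descriptive or exploratory, with no claim of component efficacy.
3. Drop in-scenario fear and perceived mental effort as hypothesised outcomes.
4. Keep STAI State with the primary outcome, which already covers anxiety; moving it into the secondary hypothesis would duplicate or demote it.
5. Reconcile the order of VR-ACT and VR-ERP between the experimental-arm section and the VR-ERP section.
6. State that the primary contrast is the effect of adding the whole VR package, including debriefing.

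The cost is protocol wording, with no added participants or visits. The downside is giving up a mechanistic claim that the design cannot support. Keeping that claim would mean randomizing the components and adding in-session ratings, at arm sizes like those in the last step of the working.

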### Design and setting of the study

The study is a two-arm randomized controlled trial with parallel, independent experimental and control groups. Both groups undergo a brief standard counseling program consisting of five individual sessions delivered by trained clinicians within the UPCS. The experimental group receives the same brief standard counseling intervention, complemented by two immersive VR modules delivered through 360° video-based scenarios: (a) a VR–Exposure and Response Prevention (VR-ERP) component providing graded and controlled exposure to anxiety-provoking public-speaking situations, and (b) a VR-Acceptance and Commitment Training (VR-ACT) component offering an ACT-based mindfulness training aimed at down-regulating physiological arousal and enhancing adaptive coping. The control group receives the standard counseling protocol only.

Psychological assessments are conducted at baseline (T0), post-treatment (T1), and at follow-up (T2), allowing evaluation of change over time and between-group differences. Physiological parameters are continuously recorded during each session to capture objective indices of arousal and recovery alongside self-report outcomes. This design enabled testing whether adding immersive, VR experiences to routine counseling provides benefits beyond standard care alone.

### Sample size

A priori sample-size estimation is conducted to determine the number of participants required to detect the expected effects of the VR-based exposure intervention on the primary outcome measures. Evidence from a systematic review [21], which examined virtual reality–based interventions targeting public-speaking anxiety in student populations, indicates that VR exposure procedures typically yield moderate-to-large reductions in anxiety symptoms compared with control or baseline conditions. Reported effects across the studies reviewed are consistent with the magnitude commonly observed in the broader VRET literature, supporting the assumption of a moderately large effect size for the planned between-group comparison.

Based on this evidence, we adopt an expected effect size of Cohen’s d = 0.75 for the between-group differences in change scores from baseline to post-intervention between the VR exposure and control groups. A power analysis conducted using G*Power 3.1 (two-tailed independent-measures t-test, α = 0.05, power = 0.80) indicated that 29 participants per group would be required to detect an effect of this magnitude.

To ensure adequate statistical power after accounting for participant attrition, commonly estimated at 15%-20% in VR-based intervention studies, we plan for an upper-bound dropout rate of 20%. Accordingly, the required number of participants is adjusted to 36 participants per group, resulting in a total target sample of 72 participants [22]. This sample size is expected to provide sufficient statistical sensitivity to detect clinically meaningful effects of the VR intervention while remaining feasible for a single-site randomized controlled trial.

### Participants and recruitment

Potential participants are identified among university students who contact the UPCS. Each student undergoes a structured screening interview conducted by a research psychologist. During this interview, the aims and procedures of the study are explained, questions are addressed, and the student’s eligibility is assessed. The screening serves to rule out conditions requiring immediate or specialized care; in such cases, students are referred to the appropriate clinical services within or outside the university, in accordance with standard UPCS referral pathways.

Eligible participants are university students aged 18 years or older who seek counseling at the UPCS and report clinically relevant anxiety in performance-related contexts, particularly public speaking.

Inclusion criteria are: (a) current enrolment at the university; (b) request for psychological counseling at the UPCS; (c) age ≥ 18 years; (d) fluency in Italian; (e) provision of written informed consent; and (f) at least moderate levels of anxiety and perceived stress as indicated by standardized measures, specifically, Personal Report of Public Speaking Anxiety (PRPSA) scores between 85 and 110 and State-Trait Anxiety Inventory (STAI) scores between 35 and 50.

Exclusion criteria are: (a) current psychotic disorder; (b) acute suicidal ideation or behavior; (c) severe substance dependence; (d) severe sensory or motor impairments that could interfere with the safe use of VR equipment; (e) inability to attend the planned sessions; and (f) concurrent participation in other specialized psychotherapy programs.

After completion of the screening interview, participants are randomized (1:1) to the experimental (counseling + VR) or control (counseling only) group using a computer-generated randomization sequence. Allocation is concealed using sequentially numbered, opaque, sealed envelopes or a password-protected electronic system, which is accessed only after participant enrollment and completion of baseline (T0) measures.

Participants are considered withdrawn from the study if any of the following occurs: (1) voluntary withdrawal at any time without the need to provide a reason; (2) emergence of adverse effects or discomfort judged to make continuation inappropriate; (3) detection of a major protocol deviation; or (4) any circumstance that, in the investigators’ clinical judgment, could compromise the participant’s health safety, or well-being. The date and reason for withdrawal will be systematically recorded in a paper-based case report form (CRF).

Recruitment is anticipated to be completed by December 2026.

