#### Psychological assessment

The protocol involves the assessment of participants through the administration of standardized self-report psychological tests designed to evaluate levels of public speaking anxiety and state and trait anxiety levels.

The instruments are:

The Italian version of the *Personal Report of Public Speaking Anxiety* (PRPSA) [23] is a self-report questionnaire designed to measure the level of anxiety individuals experience when speaking in public. The scale assesses multiple dimensions of public speaking anxiety, including cognitive, physiological, and behavioral components, capturing both anticipatory anxiety and anxiety during performance. The PRPSA consists of 34 items, each rated on a 5-point Likert scale (1 = strongly disagree to 5 = strongly agree). Items reflect feelings of tension, nervousness, and physiological arousal (e.g., “My hands tremble when I try to handle objects on the podium”), as well as negative self-appraisal and fear of audience evaluation. Total scores range from 34 to 170, with higher scores indicating greater levels of public speaking anxiety. Conventionally, scores above 131 suggest high anxiety, scores between 98 and 131 indicate moderate anxiety, and scores below 98 indicate low anxiety. The Italian version maintains strong psychometric properties, with high internal consistency (Cronbach’s α > 0.90) and good test–retest reliability. It has been validated for use among university students and adults, proving useful in both clinical and research contexts, examining performance-related social anxiety and communication apprehension.The Italian version of the *State-Trait Anxiety Inventory*,* Form Y* (STAI) [24, 25] was adopted to measure two distinct dimensions of anxiety: (i) State Anxiety (S-Anxiety), a temporary emotional condition characterized by feelings of tension, apprehension, and heightened autonomic nervous system activity, reflecting how the respondent feels at the present moment; and (ii) Trait Anxiety (T-Anxiety), a relatively stable disposition to perceive situations as threatening and to respond with anxiety across time and contexts. Each subscale consists of 20 items, rated on a 4-point Likert scale (ranging from 1 = almost never to 4 = almost always for trait anxiety, and 1 = not at all to 4 = very much so for state anxiety). Scores range from 20 to 80 for each subscale, with higher scores indicating greater anxiety levels. The Italian adaptation has demonstrated good psychometric properties, including high internal consistency (Cronbach’s α typically between 0.86 and 0.95) and construct validity consistent with the original instrument, making it one of the most widely used anxiety measures in both clinical and research settings in Italy.

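### The PRPSA entry window of 85 to 110 conflicts with the protocol's own severity bands and with its requirement of at least moderate anxiety

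*Protocol article*

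**What the plan says.** Participants and recruitment describes eligible students as those who "report clinically relevant anxiety in performance-related contexts, particularly public speaking". Inclusion criterion (f) then requires "at least moderate levels of anxiety and perceived stress as indicated by standardized measures" and puts this into numbers as "Personal Report of Public Speaking Anxiety (PRPSA) scores between 85 and 110 and State-Trait Anxiety Inventory (STAI) scores between 35 and 50".

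Psychological assessment gives the PRPSA scale and its bands: "Total scores range from 34 to 170, with higher scores indicating greater levels of public speaking anxiety", and "scores above 131 suggest high anxiety, scores between 98 and 131 indicate moderate anxiety, and scores below 98 indicate low anxiety". No other bands appear anywhere in the article, and no reason is given for either end of the 85 to 110 window.

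The STAI is described in the same section as two separate subscales, State and Trait, each scored 20 to 80. Criterion (f) gives one STAI range without saying which subscale it applies to. Neither the PRPSA nor the STAI is described as a measure of perceived stress, and Table 1 lists no stress scale.

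**The concern.** The wording of criterion (f) sets a floor and no ceiling: moderate or worse. The numbers set a floor inside the low band and a ceiling inside the moderate band, so they depart from the wording at both ends. Applied as written, a help-seeking student scoring 86 (low on the protocol's bands) meets the PRPSA limit, while students scoring 120 (moderate) or 140 (high) are refused.

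Eligibility fixes who is randomised, and no later analysis can repair it. If the numbers are followed, the trial studies a group different from the one it describes, and a reader of the results would be misled about whom they apply to. If screeners follow the words instead, entry will vary from one screener to the next.

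**Working it through.** **Inputs.** PRPSA window 85 to 110 (Participants and recruitment, criterion (f)). Bands: low below 98, moderate 98 to 131, high above 131; scale 34 to 170 (Psychological assessment).

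**Plan's own figure, checked first.** The Sample size section uses d = 0.75, two-sided α = 0.05 and power 0.80. The two-sample t-test calculation gives n = 28.90, so 29 per group (power 0.801), as stated. For 20% dropout, 29 / 0.80 = 36.25; the plan uses 36, and strict rounding up gives 37, an immaterial difference. No PRPSA limit enters this calculation, so the conflict does not change it.

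**Count of score points, both limits included.**

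| Range | Band | Points | Eligible? |
|---|---|---|---|
| 85–97 | low | 97 − 85 + 1 = 13 | yes |
| 98–110 | moderate | 110 − 98 + 1 = 13 | yes |
| 111–131 | moderate | 131 − 111 + 1 = 21 | no |
| 132–170 | high | 170 − 132 + 1 = 39 | no |

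- Share of the window that is low: 13 / 26 = 50%.
- Share of the moderate band excluded: 21 / 34 = 62%.
- Share of the high band excluded: 39 / 39 = 100%.
- Share of the moderate-to-high range excluded: (21 + 39) / (34 + 39) = 60 / 73 = 82%.
- The floor lies 98 − 85 = 13 points below the moderate threshold. The cap lies 131 − 110 = 21 points below the top of the moderate band.

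Reading the limits as exclusive (86 to 109) changes little: 12 of 24 eligible points are low, and 22 of 34 moderate points are excluded.

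**From score points to students (illustration only).** The article gives no distribution of screening scores. Assume a normal distribution F with mean 100 to 130 and SD 15 to 25, and apply a continuity correction:

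- Low share among those in the window = [F(97.5) − F(84.5)] / [F(110.5) − F(84.5)]
- Eligible share among those scoring 98 or more = [F(110.5) − F(97.5)] / [1 − F(97.5)]

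For mean 115 and SD 20, the F values at 84.5, 97.5 and 110.5 are 0.064, 0.191 and 0.411. The low share is 0.127 / 0.347 = 0.37, and the eligible share is 0.220 / 0.809 = 0.27. Across the grid, the low share runs from 15% to 49% and the eligible share from 8% to 57%.

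**The case against.** The strongest defence is that the upper limit is deliberate. The service offers five sessions, and screening refers out students who need urgent or specialist help, so a severity cap could be sensible. This stands in part: the cap cannot simply be assumed to be a mistake, and the documents do not show whether the numbers or the words are wrong. But the protocol states no such reason, no exclusion criterion names a high PRPSA score, and a cap explains neither a floor of 85 nor wording that has no upper limit.

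The bands are also presented as conventional, and the protocol does not equate a low score with anxiety that lacks clinical relevance. Participants must request counseling and report performance anxiety, and 98 to 110 is moderate. So a reader should not infer that the trial cannot answer its question. Randomisation still gives a valid comparison for those enrolled.

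Three further inferences are tempting but unsupported:

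- *Half of the participants will have low anxiety.* The 50% counts score points. The enrolled share depends on a distribution the article does not give.
- *The assumed d = 0.75 comes from a different population.* The Sample size section describes its source only as a review in student samples and gives no baseline severity.
- *The narrow window damages the analysis.* The SD of 7.5 points, √((26² − 1)/12), assumes uniform scores, for which there is no basis. Baseline variables enter only complementary models, and baseline severity as a predictor is exploratory. No effect on the primary time-by-group test has been shown.

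Finally, the full protocol may name the STAI subscale. That is a reason to treat it as a small clarification, not a separate fault.

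**Conclusion.** The contradiction is real and rests only on numbers printed in the protocol. Half of the eligible PRPSA points lie in the low band, and 60 of the 73 moderate-to-high points are shut out, including every high score. Nothing in the article reconciles the two sections.

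The harm is to the definition of the population and the reach of the conclusion, not to internal validity or the sample size. As written, the results would apply to help-seeking students with low to lower-moderate PRPSA scores, not to the at-least-moderate group the protocol names. The score-point counts need no assumption; any statement about the share of students does. It should be corrected because the threshold decides who is randomised.

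**What to change.** Reconcile criterion (f) with the PRPSA bands before further enrolment. The choice is for the investigators:

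1. **Change the limits.** Align the PRPSA limits with the stated bands and the at-least-moderate wording. Record which participants entered under the old window, so that they can be identified in the analysis and the report.
2. **Keep 85 to 110.** Describe the population as low to lower-moderate public speaking anxiety on the stated bands, give the reason for the upper limit, and restrict the conclusion to that group.

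In the same edit, state which STAI subscale the limit "State-Trait Anxiety Inventory (STAI) scores between 35 and 50" applies to, and either drop perceived stress from the criterion or tie it to a measure.

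**Cost.** Option 1 needs an ethics and registry amendment and may leave a sample enrolled under two sets of limits. Its effect on recruitment is unknown, because it depends on how screening scores are distributed. Option 2 is mainly a correction of text, with the registry entry checked for consistency. Neither adds visits or assessments, unless a stress scale is added. Recruitment is expected to end by December 2026, so the change is worth most if made soon.
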